**Fig. 1 Fig1:**
[figure not shown]
Flow-chart for patients presenting with ACS

**Fig. 2 Fig2:**
[figure not shown]
Flow-chart for patients presenting with stable coronary artery disease

The study is designed to have a total duration of 23 months, with an enrollment period of approximately 20 months. Each patient will be treated with the study drug only during the in-hospital phase, for a minimum of 3 days (Day -1 to Day 1) up to a maximum of 7 days (Day -1 to Day 5). The patient will be hospitalized (as per usual clinical practice) from Day -3 to Day -1 (admission) to Day 0–5 of the study. The total number of enrolled patients will be one hundred (*N* = 100), with a projected 10% drop-out rate and 30% of negative FFR assessment (FFR > 0.80), with a final pool comprising 60 patients who will be evaluated in terms of primary and secondary endpoints. Therefore, the study enrollment will be stopped once one hundred patients are enrolled (Fig. 3).

**Fig. 3 Fig3:**
[figure not shown]
Taper-S study flow-chart

### Sample size

This is an exploratory and pilot study, aimed at evaluating the off-target effects of ticagrelor on ischemic preconditioning. A sample size of 40–60 patients is, in general, considered appropriate for a pilot study and should provide important insights for the planning of a future larger study and for estimating confidence intervals [32]. Per our design, by assuming an absolute difference (delta) of 4 mm in the change of ST-segment shift from the first to the second balloon inflation between the two compared groups, a magnitude similar (albeit reversed) to the effect observed by Niccoli et al. in a study demonstrating the negative preconditioning effect of ethanol [33], we can infer that 30 patients per group will be required to provide an 80% power to detect a statistically significant difference between groups at a significance level set at *p* < 0.05. The standard deviation (SD) of the primary endpoint is expected to be approximately 5 to 4 mm in each treatment group. By enrolling one hundred patients, we also take into account those patients that will not require PCI after FFR evaluation (as observed in the FAME II trial) [34].

The main statistical analysis to be undertaken is a comparison of the primary endpoint (continuous variables) between the two groups of 30 patients each is a 2 × 2 analysis of variance (ANOVA) stratified by treatment group. The co-primary safety endpoint, which is a frequency value, will be analyzed using a Fisher’s exact test.

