### Study endpoints

#### Primary endpoint

The primary endpoint is the comparison of ticagrelor and clopidogrel for the delta (difference in mm) of the ST-segment elevation, as assessed by the intracoronary ECG during two-step sequential coronary balloon inflation in the index vessel.

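### The stated 80% power at 30 per group does not follow from the stated SD of 4 to 5 mm (which gives 86–97%), and the same section names a co-primary safety endpoint that the article's endpoint lists do not contain

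*Protocol article*

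**What the plan says.** The Sample size section gives every input to its calculation except sidedness:

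- Difference: "assuming an absolute difference (delta) of 4 mm in the change of ST-segment shift from the first to the second balloon inflation", compared between the two arms.
- Variability: "The standard deviation (SD) of the primary endpoint is expected to be approximately 5 to 4 mm in each treatment group".
- Type I error: "at a significance level set at *p* < 0.05".
- Result: "we can infer that 30 patients per group will be required to provide an 80% power to detect a statistically significant difference".

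The SD is attached to the primary endpoint. The Primary endpoint section defines that as "the delta (difference in mm) of the ST-segment elevation, as assessed by the intracoronary ECG during two-step sequential coronary balloon inflation", so the SD is that of the within-patient change. The thirty per group are evaluable patients: the TAPER-S trial design section reaches them from 100 enrolled "with a projected 10% drop-out rate and 30% of negative FFR assessment (FFR > 0.80), with a final pool comprising 60 patients".

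The same section also offers a pilot rationale, that 40 to 60 patients are generally considered adequate. It then adds a further endpoint: "The co-primary safety endpoint, which is a frequency value, will be analyzed using a" Fisher's exact test. The abstract and the Primary endpoint section name a single primary endpoint, the delta in ST elevation. The secondary endpoints are CFR, IMR, FFR and angina score. Neither list contains a safety endpoint.

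**The concern.** Difference, SD, alpha, power and group size are tied by one equation. Once four are given, the fifth is fixed. Here all five are printed and they do not agree, so at least one is wrong or an input is missing. The SD matters most. The section says the pilot should inform a larger study, and required numbers scale with the SD squared: moving from 4 to 5.4 mm multiplies a sample size by (5.4/4)² ≈ 1.8.

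The co-primary label is a different kind of problem. How many primary endpoints a trial has is a protocol matter, and this article gives two answers. If a second primary endpoint exists, the reader needs to know which event it is, whether either or both must succeed, and how alpha is divided. The calculation contains no event rate, safety difference or alpha allocation.

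**Working it through.** **Inputs.** Δ = 4 mm; SD 4 to 5 mm per arm, applied to the change; α = 0.05; 30 per group (all from Sample size); 1:1 allocation (Randomization). Two-sidedness is assumed. The between-arm test on the change is treated as a two-sample t-test. In a 2 × 2 ANOVA of arm by inflation, the arm-by-inflation term is the same test.

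**Step 1: try to reproduce 30 per group.** Normal approximation: n per group = 2 (z₀.₉₇₅ + z₀.₈₀)² SD² / Δ², with (1.960 + 0.842)² = 7.849.

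- SD 5: 2 × 7.849 × 25 / 16 = 24.5, so 25. The exact t calculation gives 26.
- SD 4: 2 × 7.849 × 16 / 16 = 15.7, so 16. The exact t calculation gives 17.

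Neither is 30. A one-sided test moves further away (20 and 13 by the normal approximation).

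**Step 2: power at 30 per group.** Standard error = SD × √(2/30); noncentrality = 4 / SE; 58 degrees of freedom.

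| SD (mm) | SE | 4 / SE | Power (t) | n per group for 80% (t) |
|---|---|---|---|---|
| 4 | 1.033 | 3.87 | 96.8% | 17 |
| 4.5 | 1.162 | 3.44 | 92.3% | 21 |
| 5 | 1.291 | 3.10 | 86.1% | 26 |
| 5.4 | 1.394 | 2.87 | 80.5% | 30 |

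If one arm has SD 5 and the other SD 4, the pooled SD is √((25 + 16)/2) = 4.53 and power is 92%.

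**Step 3: what would make the stated pair true?**

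- At α = 0.05 two-sided, the SD that gives exactly 80% at 30 per group is 5.44 (t) or 5.53 (normal approximation). Both lie outside the stated range.
- Keeping SD 4 to 5, the difference detectable with 80% power at 30 per group is 2.9 mm (SD 4) to 3.7 mm (SD 5), not 4 mm.
- With α = 0.025 two-sided and SD 5, the normal approximation gives 29.7, so 30 per group. The t calculation gives 31, with 78.5% power at 30. A Bonferroni split over two primary endpoints would produce this, but the section states 0.05.

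**Step 4: does attrition explain it?** No. 100 × (1 − 0.10 − 0.30) = 60, or 100 × 0.9 × 0.7 = 63. Either leaves at least 30 evaluable per group on average, so 30 is already net of losses.

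**Step 5: the endpoint lists side by side.** Abstract: one primary (delta ST); secondary CFR, IMR, FFR and angina score. Primary endpoint section: delta ST only. Secondary endpoints section: CFR, IMR, FFR and angina score. Statistical analysis section: a primary comparison of delta ST, with no safety endpoint named. Sample size section: a co-primary safety endpoint, described only as a frequency. The last does not fit the others.

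**The case against.** The strongest reply is that nothing operational is wrong. Thirty per group exceeds the 17 to 26 that the inputs require, and 60 evaluable patients also satisfy the separate pilot rationale. Both points stand: the error is conservative and no patient number depends on correcting it. If 5.4 was meant, the arithmetic is right and only the SD wording is wrong. That is plausible, because the range is printed in descending order, but the text does not settle it. Nor must a later study inherit the planning SD, since it would use the SD the pilot observes.

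A reader might infer that the trial is underpowered by taking 4 to 5 mm as the SD of a single inflation reading. Power at 30 per group would then depend on the within-patient correlation: 58–77% at correlation 0, 86–97% at 0.5. The text gives the SD to the primary endpoint, which is the change, so this is not its reading.

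A reader might also try to price the co-primary by taking dyspnoea at the Background's 38.6% versus 9.3%, giving a joint power of 0.86 × 0.69 = 0.60, or an error rate near 10% if either endpoint sufficed. The documents support neither:

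- Nothing makes dyspnoea the co-primary. It is scored on a Borg scale, and the rates come from another study.
- Joint success has no sensible meaning when success on the safety side would be proof of harm.
- The 0.69 assumes 30 per group, but dosing begins before FFR. With 50 randomised per group, Fisher's power at those rates is 0.92.
- Fisher's test is conservative. At 30 per group its true size is 0.8% at a common rate of 9.3% and 2.7% at 50%. With an independent 5% test, the total is 1 − 0.95 × 0.992 = 5.8% to 1 − 0.95 × 0.973 = 7.6%.

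Finally, the article is condensed, and it refers adverse-event definitions to Additional file 1, which is not shown. The claim is therefore limited to the endpoint lists in the article.

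**Conclusion.** The point holds in two limited parts.

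First, the power statement is wrong on its own inputs. At 4 mm, SD 4 to 5 mm and two-sided 0.05, 30 per group gives 86–97% power, and 80% needs only 17 to 26 per group. The nearest stated SD misses by 4 patients per group and 6 percentage points of power, which is more than rounding. The stated pair needs an SD of about 5.4 mm, or is approximately met by an alpha of 0.025 at SD 5. Which of these lies behind the figure cannot be told from the article. The result rests on a two-sided test and on the SD being that of the change.

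Second, the co-primary safety endpoint contradicts the single primary endpoint given elsewhere in the article. Its effect on error rate or power cannot be sized, because the endpoint, its event rate and its decision rule are not stated in the text shown. Whether it is stray text or a real endpoint is for the sponsor to say.

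**What to change.** In the Sample size section, print one set of figures that agree, and state that the test is two-sided:

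- SD about 5.4 mm, 4 mm difference, 30 per group, 80% power; or
- SD 4 to 5 mm, 4 mm difference, 30 per group, 86–97% power, adding that the difference detectable with 80% power is 2.9–3.7 mm; or
- if alpha was split, the alpha given to the ST endpoint and the SD used, with the power recomputed (78.5% by the t-test for 0.025 and SD 5 at 30 per group).

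Then reconcile the endpoint hierarchy. Either drop the co-primary label and report safety as a descriptive outcome with a 95% CI, leaving delta ST as the sole primary endpoint, or define the safety endpoint, its alpha and its decision rule, and list it with the primary endpoint.

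The power correction is wording only: 100 enrolled and 60 evaluable stay as they are. Dropping the label is also wording only. Keeping a real co-primary would take a short added specification and a power statement for it.

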### Study population

Patients will be required to have a clinical indication to undergo scheduled FFR-guided PCI. Two types of patients will be included:
Patients presenting initially with an ACS, with an intermediate coronary lesion (40–80% in severity, where functional evaluation with FFR must be used based on clinical situation) in a nonculprit artery, thus requiring a staged FFR-guided PCI (at least 1 month after the index ACS event)Patients with a stable CAD and who are undergoing scheduled FFR-guided PCI of any vessel

### Patient selection

#### Inclusion criteria

The inclusion criteria are as follows:
Signed and dated written Informed Consent obtained prior to the inclusion in the trialAge ≥ 18 and ≤ 75 yearsWeight ≥ 60 kgPatients must have a clinical indication to undergo scheduled FFR-guided PCI (the two types of patients to be included are noted in 5 and 6)Patients presenting initially with an ACS, with an intermediate coronary lesion (40–80% in severity, where functional evaluation with FFR must be used based on clinical situation) in a nonculprit artery, thus requiring a staged FFR-guided PCI (at least 1 month after the index ACS event);Patients with a stable CAD undergoing scheduled FFR-guided PCI of any vesselPatients already may be on the antiplatelet-directed treatment with either ticagrelor (previous ACS patients) or clopidogrel (stable patients)

#### Exclusion criteria

The exclusion criteria are as follows:
Known hypersensitivity to aspirin, clopidogrel, ticagrelor, or any similar drugConcomitant oral anticoagulant therapy, or need for it (e.g., atrial fibrillation, mechanical valve, etc.)Need for a concomitant cardiac noncoronary procedure, such as valve repair or replacementAny previous history of ischemic stroke, intracranial hemorrhage or disease (neoplasm, arteriovenous malformation, or aneurysm)Any active pathological bleeding or history of significant gastrointestinal bleeding, genitourinary bleeding or other site abnormal bleeding within the previous 3 months, other bleeding diathesis, or considered by the Investigator to be at high risk for bleedingConcomitant oral or intravenous (IV) therapy with strong CYP3A inhibitors, CYP3A substrates with narrow therapeutic indices, or strong CYP3A inducers. Any of such concomitant treatment will be mapped and evaluated by the Investigator to comply with the exclusion criteriaIncreased risk of bradycardia eventsKnown pregnancy and/or breast-feedingSevere uncontrolled chronic obstructive pulmonary diseaseConcomitant theophylline/aminophylline useBaseline ECG with significant conduction abnormalities (i.e., left ventricular hypertrophy with repolarization abnormalities, left bundle branch block, etc.)Evidence of prior myocardial infarction by cardiac imaging in the territory of the index vesselReduced left ventricular systolic function at screening/randomization (left ventricular ejection fraction < 40% within 48 h before index PCI, as assessed by transthoracic echocardiography)Clinical and laboratory signs of congestive heart failurePresence of coronary collaterals on diagnostic coronary angiographyDiffuse obstructive disease (≥ 70% stenosis) in the distal segment of the target vesselLeft main and/or three-vessel CADEnd-stage renal disease (as assessed by the estimated glomerular filtration rate CKD-EPI formula, eGFR < 15 mL/min./1.73 m^2^)Documented severe hepatic impairment (e.g., elevated liver enzymes, cirrhosis, etc.)

### Study drugs

#### Dosing, posology, and route of administration

Ticagrelor will be given in a loading dose of 180 mg (on Day -3 to -1), followed by a dose of 90 mg twice daily (from Day 0 to discharge between Days 1 to Day 5, during the index hospitalization). If the patient is chronically on ticagrelor, the loading dose will be omitted. In case of missed dose, the lapses in therapy should also be avoided. A patient who misses a dose of ticagrelor should take only one tablet (their next dose) at its scheduled time.

Clopidogrel will be given in a loading dose of 600 mg (on Days -3 to -1), followed by a dose of 75 mg once a day (from Day 0 to discharge during Days 1 to Day 5, during the index hospitalization). If the patient is chronically on clopidogrel, the loading dose will be omitted. The antiplatelet switch will be managed according to generally agreed consensus. The details of the Antiplatelet Drug “switch” are specified in the section below.

#### Antiplatelet drug switch

Patients could be randomized while on treatment to either ticagrelor (previous ACS patients) or clopidogrel (stable patients). For those on long-term ticagrelor or clopidogrel treatment randomized to the corresponding drug, no loading dose will be given, and the patient will be continued on the respective drug. For those randomized to the noncorresponding group, the most recent recommendations regarding antiplatelet drug “switch” will be followed [35, 36] - a loading dose of the other drug will be given, 12–24 h before the scheduled PCI procedure. For patients previously on a long-term ticagrelor treatment, a 24-h washout period (i.e., the withdrawing of a single dose) will be applied before clopidogrel loading dose is initiated, to aid in clearance of the reversible platelet inhibition by ticagrelor and its main metabolite [36]. For both ticagrelor and clopidogrel, the last drug dose will be given at least 4 ± 1 h before the start of the index procedure [37]. After the index procedure, long-term antiplatelet treatment will be administered according to the most recent guidelines [38]. Timing and schedule of all the procedures projected during the protocol visits are detailed in the flow chart table that is available below. See also Additional file 1 for details related to main pharmacological interactions and adverse events definition and reporting.

### Compliance

Given that the administration of the drugs is conducted while the patients are hospitalized, the compliance to the treatment scheduled must be considered by default as 100% endorsed. Nevertheless, in case any of the requested doses are not to be administered, the issue and the relevant reason will be documented by the Investigator (and/or his delegates) on the appropriate source document.

### Discontinuation/stopping of the treatment

Enrolled subjects may be discontinued from the investigational product (IP) in case of consent withdrawal, any adverse event, and non-compliance to study protocol or incorrect enrollment.

### Data collection and management

The referent and person responsible for the coordinating center, Fondazione Policlinico Universitario Agostino GemelIi, will be [name], PhD. The source data, recorded in the appropriate source documentation, will be reported by the Principal Investigator and/or his delegates in a web-based database (electronic case report form, eCRF). The validation of the inconsistencies (change or acceptance) will be made by the Principal Investigator and/or his delegates. Before the data freezing, the person in charge of the data management will code the medical terms. Data will be collected by their registered delegates and will be stored in dedicated paper file, which will be locked for security. The electronic data (the eCRF) will be password secured.

### Inspections

The Principal Investigator and/or his delegates must allow the regulatory authorities to conduct inspections. The inspection on the part of the Regulatory Authority consists of an official review of the documents, facilities, records, and any other resource considered by the authority to relate to the study. Auditing of the trial conduct will be performed according to the CTC Quality System and will be independent from investigators and the sponsor.

## Study procedures

### Visit scheduling

Patients satisfying inclusion criteria and having none of the exclusion criteria will be randomized to either ticagrelor or clopidogrel (Figs. 1 and 2). Ticagrelor will be administered in a loading dose of 180 mg followed by a dose of 90 mg twice daily. Clopidogrel will be administered in a loading dose of 600 mg, followed by a dose of 75 mg once a day. If the patient is chronically on ticagrelor or clopidogrel treatment, the loading dose will be omitted.

All patients will receive acetylsalicylic acid (aspirin) at a dose of 75 to 100 mg daily. For those who had not previously been receiving aspirin, 250 or 325 mg will be the preferred loading dose. The study drug will be continued for at least 72 h before the second PCI.

During PCI, two sequential balloon inflations will be performed to measure ischemic preconditioning. Operators will measure the degree of ST-segment elevation by intracoronary ECG and by surface ECG during coronary balloon inflation.

### Randomization

Patients will be randomly assigned to **ARM A (clopidogrel)** or **ARM B (ticagrelor)** in a 1:1 ratio. The allocation to the assigned treatment arm will be known to the patients and to the Principal Investigator (PI) and/or his delegates.

The randomization will be performed at Visit 0. Randomization process will be performed printing 50 tags reporting the word *“Ticagrelor”* and 50 tags reporting the word *“Clopidogrel”* inserted into anonymous white letter envelopes; the envelopes will be mixed and then stacked up in random order, with the opening side toward the bottom of the pile, by the study monitor; the resulting random sequence of 100 envelopes will be consigned to the PI or his delegates, which are entrusted with their preservation and responsible for any adulteration. At visit 0 the PI or his delegates will open the first available envelope, proceeding from top to bottom of the pile. The already opened envelopes will be stored separately from the others and will be available to the study monitor on request.

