## Materials/Methods

### TAPER-S trial design

This study is a prospective, randomized, blinded, end-point trial that will enroll patients with multivessel CAD requiring scheduled treatment of a second lesion located in a nonculprit vessel. The typical patient will be a patient with purely stable CAD and a scheduled, FFR-guided PCI of any vessel. Patient presenting initially with an ACS, with an intermediate coronary lesion (40–80% in severity, where functional evaluation of the stenosis with FFR must be used based on clinical situation) in a nonculprit coronary artery, for whom a delayed, FFR-guided strategy is chosen, may also be included in the study. In these patients, recovery of the microvascular function requires that at least 1 month has elapsed before re-evaluation of the culprit lesion, as FFR in the acute phase is known to be unreliable [31]. Screening/randomization will take place 1 to 3 days before the index procedure. Randomization will be blocked within each study site, which will allow an even balance of patients to be randomized to either drug at each recruiting center. Patients with FFR > 0.80 (no functionally significant stenosis) will be excluded from the study (Figs. 1 and 2). The study will be conducted in Italy, involving A. Gemelli Polyclinic of the Catholic University of the Sacred Heart in Rome and Grosseto Hospital (Ospedale della Misericordia Grosetto) in Grosetto, Italy.

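### The design section states blocking within site, but the envelope procedure is one unblocked pile of 100, so site balance is not delivered and concealment is only weakly protected

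*Protocol article*

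**What the plan says.** The section on trial design states: "Randomization will be blocked within each study site, which will allow an even balance of patients to be randomized" to either drug at each centre. It names two centres, "in Rome and Grosseto Hospital".

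The Randomization section gives the working procedure. Fifty tags per drug are "inserted into anonymous white letter envelopes", mixed, and "stacked up in random order, with the opening side toward the bottom of the pile, by the study monitor". Then "the resulting random sequence of 100 envelopes will be consigned to the PI or his delegates", who are also answerable for any tampering. At Visit 0, "the PI or his delegates will open the first available envelope, proceeding from top to bottom of the pile". Opened envelopes are stored apart and can be shown to the monitor on request. The same section says: "The allocation to the assigned treatment arm will be known to the patients and to the Principal Investigator (PI) and/or his delegates".

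Elsewhere, total enrolment is fixed at 100, with about 60 expected to be evaluable (trial design), and the PCI operators are blinded to arm (Abstract, Methods).

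**The concern.** The two sections describe different randomisation schemes, and a reader cannot tell which one was used. The operating procedure contains neither blocks nor a site split, so the property claimed in the design section (even numbers of each drug at each centre) does not follow from it.

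The second issue is custody. The investigator or delegates hold the sequence, open it and answer for its integrity, and they know every earlier allocation. The article itself shows why a recruiter might care about the next envelope. Patients may arrive on ticagrelor (after an ACS) or on clopidogrel (stable disease), and allocation to the other drug triggers a switch with a loading dose and, coming from ticagrelor, a washout. Prior drug tracks patient type, so any steering would be systematic rather than random.

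At stake are possible selection at enrolment and possible confounding of the treatment comparison with site.

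**Working it through.** **1. Is the pile one site's list or the whole trial?** Envelopes: 50 + 50 = 100. Total enrolment: 100. Evaluable: 100 × (1 − 0.10 − 0.30) = 60, as the article states. The pile is therefore the whole trial. It cannot be one hospital's blocked list with a second list left undescribed.

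**2. Within-site balance under the single pile.** If a site draws *m* of the 100 envelopes, its ticagrelor count *k* is hypergeometric (100 envelopes, 50 per drug, *m* drawn). The arm difference is 2*k* − *m*, with

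SD = 2 × √[*m* × 0.25 × (100 − *m*)/99].

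For *m* = 30: 2 × √(30 × 0.25 × 70/99) = 2 × 2.30 = 4.6 patients. The article gives no site sizes, so a range is shown for the site concerned.

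| Patients at site (assumed) | SD of arm difference | P(≥ 4) | P(≥ 6) | P(≥ 8) |
|---|---|---|---|---|
| 10 | 3.0 | 32% | 9% | 2% |
| 20 | 4.0 | 45% | 21% | 8% |
| 30 | 4.6 | 51% | 28% | 13% |
| 40 | 4.9 | 54% | 31% | 15% |
| 50 | 5.0 | 55% | 32% | 16% |

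A difference of 6 is 18:12 at a site of 30 and 13:7 at a site of 20.

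**3. Within-site balance under blocking.** With permuted blocks inside a site, the difference never exceeds half the block size: 2 for blocks of 4, 3 for blocks of 6 (block sizes assumed; none is given).

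**4. Does the cap survive to the analysed patients?** No. About 40% are expected to leave after randomisation. Simulating a site of 30 with each patient retained independently with probability 0.6, the evaluable arm difference is 4 or more in about 21% of trials with blocks of 4 and in about 36% with the single pile. Blocking still helps, but the gain is smaller than the randomised counts suggest.

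**5. Predictability by counting.** Someone who tracks opened envelopes and always guesses the drug with more left is right for about 55.8 of 100 patients and 7.0 of the last 10, against 50 and 5 by chance (20,000 simulated piles). That is modest. Known fixed blocks of 4 would be worse: the expected correct guesses per block are 1/2 + 2/3 + 2/3 + 1 = 2.83 of 4, or about 71 of 100. Counting is therefore not the main weakness of the pile. The weakness is that the order exists, as described, only as the physical stack in the recruiters' hands. This also shows why blocked lists must have undisclosed, varying block sizes.

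**The case against.** Several points on the other side are fair.

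- **Safeguards exist.** The monitor, not the investigator, shuffles and stacks the pile with the openings facing down. The rule is first envelope from the top, opened envelopes are kept, and auditing is independent of investigators and sponsor (Inspections). These stand as partial protection. None of them fixes the original order in a record held outside the recruiting team.
- **Blinded operators and a within-patient endpoint.** Operators, who measure the ST shift, are blinded, and the endpoint is a difference between two inflations, so a constant site effect on the ECG level should largely cancel. This limits measurement bias. It does not prevent selection at enrolment, nor a site effect on the size of the change itself.
- **One pile might serve both hospitals.** The article does not say where the pile is kept, and a coordinating centre could open envelopes for both. The allocation would still not be blocked by site.
- **Chance site imbalance is not bias**, and this is an exploratory pilot. Agreed: the single pile does not by itself invalidate the 1:1 comparison or inflate type I error.

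A reader might also infer more than the article supports. It never promises allocation concealment, so none has been promised and broken. It does not say that the envelopes are unnumbered, unsealed or transparent; it is silent, and the full protocol may specify this. Nor does the Statistical analysis section require a randomisation list before envelopes are opened. It expects one in SAP Version 2.0, after the Data Review Meeting, and a list compiled from opened envelopes would satisfy that.

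**Conclusion.** The contradiction stands, and no reading reconciles the two sections: a single shuffled pile covering all 100 patients is not blocking within site. Followed as written, it does not deliver the stated balance at each centre. For an assumed site of 30, an arm difference of 6 or more among randomised patients has a 28% chance (21% for a site of 20), against a maximum of 2 under assumed within-site blocks of 4. That cap does not carry over to the roughly 60 evaluable patients.

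Concealment is weakly protected as described, because unblinded recruiters keep, police and open the pile and no independently held record of its order is described. This is a finding about exposure. It does not show that any envelope was previewed, skipped or reordered. The harm is possible selection bias and confounding by site. It still warrants correction in a pilot, because the method of allocation underlies every comparison in the trial.

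**What to change.** Reconcile the trial design and Randomization sections by replacing the single pile for patients still to be randomised:

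- one permuted-block list per hospital, computer-generated, with varying and undisclosed block sizes, produced and held away from recruiting staff (by the monitor or centrally);
- release of one allocation at a time, after eligibility is confirmed, through central or web allocation or through sequentially numbered, opaque, sealed envelopes specific to each site;
- existing allocations kept, with a written account of how they were made, including where the pile was held and how the second hospital drew from it;
- site as a fixed effect in the primary model.

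The cost is a short amendment and a small allocation set-up, with no extra patients or procedures. The eCRF is described only as a data-capture database, so an allocation function there cannot be taken for granted; site-specific envelopes are the fallback. Balance among patients already randomised cannot be restored. Enrolment was expected to finish by the end of 2019 (Trial status), so if few or no patients remain, the documentation and the site term are what can still be gained.
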